**Interviews with ASSET research team, reflections on project, after one year**

- How does the telehealth intervention change equity, equality, empowerment, trust among clinicians, monitoring of patients in their home, effect of surveillance, therapeutic or dehumanizing effect, different meanings of information? 5
- To what extent does the information system meet the project’s requirements as well as objectives?3
- What can be generalised/transferred to another study/setting?5
- **R**eview thoughts, feelings, behaviour linked to planned and unplanned action
- **E**xceptions when everything appears to be going well
- **F**uture impact such as identifying the next step in our activities
- **L**earn as we consider opportunities for building models and enhancing our understanding
- **E**xplanations when things are in apparent disagreement
- **C**hallenge assumptions and consider
- what **T**roubles or puzzles us about our observations (Day, Orr, Sankaran & Norris 8)

# Appendix 4. Adverse Effect adjudication process and reporting

Hospitalization, Prolonged Hospitalization or Surgery

Neither the condition, hospitalization, prolonged hospitalization, nor surgery are reported as an adverse event if they are for diagnostic or elective surgical procedures for a pre-existing condition. Surgery should ***not*** be reported as an outcome of an adverse event if the purpose of the surgery was elective or diagnostic and the outcome was uneventful.

Recording

At each contact with the subject, the researcher must seek information on adverse events by specific questioning. Information on all adverse events should be recorded immediately in the source document, and also in the appropriate adverse event section of the case report form (CRF). Where an adverse event occurs between interviews, the Study Manager coordinators will provide the local researcher with the adverse event information.

Report to Study Manager within 1 month

At the time of the initial report, the following information should be provided:

| - Subject number - A description of the event - Date of onset - Current status - The reason why the event is classified as serious - Researcher assessment of the association between the event and study participation |
| --- |

Within the following 48 hours, the researcher must provide further information on the serious adverse event in the form of a written narrative. This should include a copy of the completed Serious Adverse Event form, and any other diagnostic information that will assist the understanding of the event.

Participant Withdrawal

A withdrawal is defined as a withdrawal of consent to participate post-randomisation. The researcher will request the opportunity to ask the client or next of kin some questions after four months and then after 12 months to ascertain if they are alive and where they are residing. The older person or next of kin will have right of refusal.

Medical Monitoring

safety monitoring will include careful assessment and appropriate reporting of adverse events as noted above, as well as the construction and implementation of a site data and safety-monitoring plan. Medical monitoring will include a regular assessment of the number and type of serious adverse events.

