# Adverse event reporting

All of the people enrolled in this study are under ‘usual care’ – from their general practitioner and / or hospital specialists - with or without the addition of telecare. Given that the participants are either unwell or may become unwell, possibly at short notice, we must allow for the possibility that introducing telecare may disrupt care in ways not anticipated.

Adverse events to be recorded and assessed by independent review, for intervention group only, within 6 months of enrolling in study:

1. Death
2. Unplanned hospitalisation or prolongation of hospitalisation
3. Patient withdraws from study

A **Data and Safety Monitoring Board Panel** (DSMP) will be appointed to undertake and / or oversee these reviews. The Panel will include clinical, research and statistical skills. Analyses will be un-blinded.

See **Appendix 2** for adjudication process and reporting

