**Data and document handling**

The following table outlines the flow of information from recruitment to assessment.

Table 1: summary of data and document handling

| **Record** | **Data handling procedure** |  |
| --- | --- | --- |
| Eligible clients list | Stored electronically by local researcher; emailed to Study Manager weekly |  |
| Ineligible clients list | Stored electronically by local researcher; emailed to Study Manager weekly |  |
| Contact list | Stored electronically by local researcher; emailed to Study Manager weekly |  |
| Declined clients list | Stored electronically by local researcher; emailed to Study Manager weekly |  |
| Delayed Interview list | Stored electronically by local researcher; emailed to Study Manager weekly |  |
| Randomisation list | Auckland and Counties Manukau: researcher phones randomization service while still with patient, records on Care Report Form, updates local list of Intervention and Control patients, emails Study Manager within 24 hours.  Canterbury: researcher confirms general practice of patient, confirms and records Intervention or Control group, emails Study Manager within 24 hours. |  |
| Enrolled participant list | Local researcher maintains up-to-date list; emails to Study Manager weekly |  |
| Participant contact card | Local researcher maintains up-to-date list; emails to Study Manager weekly |  |
| Withdrawn participant list | Local researcher maintains up-to-date list; emails to Study Manager weekly |  |
| Participant research interview (CRF = Case Report Form) | Local researcher keeps original, faxes or emails Study Manager weekly. Transfers originals to Study Manager at end of study. |  |
| Interview recordings | Digital recording and field notes sent to Study Manager within 24 hours. |  |

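### Appendix 4 allows a month for the first adverse event report, deaths and serious events included, a looser limit than the weekly one for routine data

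*Protocol*

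**What the plan says.** The Adverse event reporting section lists three events for independent review: death, an unplanned or prolonged hospital stay, and withdrawal. They are recorded "for intervention group only, within 6 months of enrolling in study". The stated reason for the review is that "we must allow for the possibility that introducing telecare may disrupt care in ways not anticipated".

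Appendix 4 then gives the route:

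- Events are entered at once in the source document and in the adverse event part of the case report form (CRF).
- The limit for telling the centre is "Report to Study Manager within 1 month".
- The first report must include "The reason why the event is classified as serious", so serious events fall under the same limit.
- The next step is "Within the following 48 hours, the researcher must provide further information on the serious adverse event in the form of a written narrative".
- For events between interviews, the Study Manager's coordinators inform the local researcher. No time limit is given for that step.

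Table 1, under Data and document handling, gives the rhythm for other records. For the interview CRF it says "Local researcher keeps original, faxes or emails Study Manager weekly". The list of withdrawn participants also goes weekly. For the randomisation result the rule is "emails Study Manager within 24 hours".

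**The concern.** The monitoring panel exists to notice unforeseen harm from telecare, and the only upward safety report with a stated limit goes through the Study Manager. That limit therefore bears on how soon the panel can have the researcher's account of an event, including why it is serious and whether it is linked to participation. A month is long against a loan of three months with new patients starting every month. It is also out of step with the protocol's own practice, since the same researcher sends ordinary study records to the same person every week. The short 48-hour step adds little urgency because it waits for the slow step before it. With no start date for the clock, two sites could apply the month differently and both comply.

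**Working it through.** The reporting limit is a rule with no calculation behind it, so the check compares it with the protocol's other time frames.

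**Inputs**

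- Limit for the first report: 1 month (Appendix 4). Taken as 365.25/12 = 30.44 days.
- Routine transmission: 7 days (Table 1).
- Loan length: up to 3 months (Study Design); 6 months for Canterbury and Tairawhiti (Appendix 8).
- New telecare patients per month: 4, 4, 4 and 2 at the four sites, over 12 months of recruitment (Appendix 8).
- Telecare patients: 48 at each of the three randomised sites (Appendix 8).
- Death rate in COPD and heart failure: about 20% per year (Statistical Issues).

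**Lag as a share of the loan**

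- 1 month / 3 months = 33.3%. With the 48-hour narrative added: (30.44 + 2) / 91.31 = 35.5%.
- 1 month / 6 months = 16.7%. With the narrative: (30.44 + 2) / 182.63 = 17.8%.
- Weekly limit: 7 / 91.31 = 7.7% of a 3-month loan; 7 / 182.63 = 3.8% of a 6-month loan.

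These shares count from the start of the clock. If the month runs from awareness, the lag from onset can be longer.

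**Patients who can start before the report is due**

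- 4 + 4 + 4 + 2 = 14 in one month.
- Under a weekly limit, assuming even intake: 14 × 7 / 30.44 = 3.2.
- This applies while recruitment lasts. After the last intake no further patients start.

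**How often the route will be used**

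- Six-month mortality at a constant hazard: 1 − 0.8^0.5 = 10.6%.
- Per randomised site: 48 × 0.1056 = 5.1 deaths.
- Three sites: 144 × 0.1056 = 15.2 deaths, over 12 months of recruitment plus 6 of follow-up. 15.2 / 18 = 0.8 per month on average.
- Hospital stays and withdrawals come on top. The protocol gives no event rate for unplanned stays in these patients.

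The deaths are background mortality under the protocol's own assumption. They show that the route will be used and say nothing about harm from telecare.

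**Limits side by side**

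| Record | Limit to the Study Manager |
| --- | --- |
| Randomisation result | 24 hours |
| Interview CRF | weekly |
| Withdrawn participants | weekly |
| First adverse event report, deaths and serious events included | 1 month |

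Withdrawal appears twice: weekly as a list entry, and within a month as an adverse event.

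**The case against.** The strongest reply is that the month is an outer limit for a structured report and not the time before the centre hears anything. An event found at an interview is entered at once on a CRF that goes out weekly. For events between interviews, information comes from the Study Manager's coordinators, so the centre already knows. This stands, and it rules out the inference that nobody outside the site is told for a month. It does not cover everything: Table 1 ties the weekly transfer to the interview CRF, and a researcher may learn of an event outside an interview, for example during an observation session.

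Other strong readings also fail:

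- A reader might infer that the limits contradict each other. They do not. A weekly data transfer and a formal report within a month can both be met, and a list entry and an event report are different records.
- A reader might infer that the slowest limit is reserved for the gravest events. The limit is the same for all events, and serious ones carry the extra narrative.
- The report on an event first known centrally may look circular. It still adds the researcher's view of association and seriousness, which the coordinators' notice is not said to contain.
- A reader might infer that review usually comes after the affected patients have finished. If events are spread evenly over a 3-month loan and the full month is used, a third are reported after the loan ends; over a 6-month loan, a sixth.

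It is also fair to say that the protocol gives no meeting interval for the panel, and that a site safety-monitoring plan it mentions is not shown and may set timings. A month in place of a week therefore cannot be shown to change any particular review. Patients remain under their usual doctors throughout, so their immediate care does not wait for this report.

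**Conclusion.** The point holds as a misalignment worth correcting. The protocol sets a single one-month limit for the first adverse event report, with no shorter limit for deaths or serious events and no start to the clock. The same researcher already sends routine records weekly. At most, the lag is a third of a 3-month loan, or a sixth where Appendix 8 shows 6 months, and one further monthly intake of 14 can begin within it. A weekly limit would cut the lag to 7.7% or 3.8% of the loan.

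These figures assume that the full month is used, that no other route brings the event sooner, and that intake follows Appendix 8. The two loan lengths are themselves inconsistent between Study Design and Appendix 8 and must be reconciled; the point holds under either. Nothing here shows that patients would be harmed by the delay. The case rests on a loose rule in the safety route that can be tightened at almost no cost.

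**What to change.** In Appendix 4:

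- Replace the one-month limit with one no longer than the weekly transmission in Table 1.
- State the start of the clock: the researcher's awareness of the event or, for events first known centrally, the date on which the coordinators notify the researcher.
- Keep the 48-hour narrative running from the first report. If it ran from awareness, it could fall due before the first report.
- Keep the researcher's assessment of association for every event, including those that the centre knew first.

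In Table 1, add a row for the adverse event report with the same limit, and say how it relates to the weekly CRF and the list of withdrawn participants.

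This is a change of wording that uses emails already planned. The cost is slightly more prompt paperwork for the local researcher. It does not affect the design, sample size or analysis.

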# Appendix 5. Study flow diagrams Auckland, Counties Manukau and Canterbury

[figure not shown]

# Appendix 7. Study flow diagram Tairawhiti

[figure not shown]

Note detail refinements from [name] email 24 Nov

# Appendix 8. Workload and equipment needed by month

| **Auckland** |  |  |  |  |  |  |  |  |  |  |  |  |  |  |  |  |  |  |
| --- | --- | --- | --- | --- | --- | --- | --- | --- | --- | --- | --- | --- | --- | --- | --- | --- | --- | --- |
|  |  |  |  |  |  |  |  |  |  |  |  |  |  |  |  |  |  |  |
| Patient numbers in active and control arm, with tallies for clinical load, equipment numbers, researcher load | | | | | | | | |  |  |  |  |  |  |  |  |  |  |
| **equipment used 4 times, 3 months per patient** | | |  |  |  |  |  |  |  |  |  |  |  |  |  |  |  |  |
| recycle equipment starts Jun 10 | |  |  |  |  |  |  |  |  |  |  |  |  |  |  |  |  |  |
|  |  |  |  |  |  |  |  |  |  |  |  |  |  |  |  |  |  |  |
|  | **Mar-10** | **Apr-10** | **May-10** | **Jun-10** | **Jul-10** | **Aug-10** | **Sep-10** | **Oct-10** | **Nov-10** | **Dec-10** | **Jan-11** | **Feb-11** | **Mar-11** | **Apr-11** | **May-11** | **Jun-11** | **Jul-11** | **Aug-11** |
| **Clinical load** |  |  |  |  |  |  |  |  |  |  |  |  |  |  |  |  |  |  |
| recruitment total | 8 | 8 | 8 | 8 | 8 | 8 | 8 | 8 | 8 | 8 | 8 | 8 |  |  |  |  |  |  |
| recruitment to intervention | 4 | 4 | 4 | 4 | 4 | 4 | 4 | 4 | 4 | 4 | 4 | 4 |  |  |  |  |  |  |
| intervention total current | 4 | 8 | 12 | 12 | 12 | 12 | 12 | 12 | 12 | 12 | 12 | 12 | 8 | 4 |  |  |  |  |
|  |  |  |  |  |  |  |  |  |  |  |  |  |  |  |  |  |  |  |
| **Equipment load** |  |  |  |  |  |  |  |  |  |  |  |  |  |  |  |  |  |  |
| equipment in use | 4 | 8 | 12 | 12 | 12 | 12 | 12 | 12 | 12 | 12 | 12 | 12 | 8 | 4 |  |  |  |  |
|  |  |  |  |  |  |  |  |  |  |  |  |  |  |  |  |  |  |  |
| **Researcher load** |  |  |  |  |  |  |  |  |  |  |  |  |  |  |  |  |  |  |
| new patient training | 4 | 4 | 4 | 4 | 4 | 4 | 4 | 4 | 4 | 4 | 4 | 4 |  |  |  |  |  |  |
| patient baseline assessment | 8 | 8 | 8 | 8 | 8 | 8 | 8 | 8 | 8 | 8 | 8 | 8 |  |  |  |  |  |  |
| patient 3 month assessment |  |  |  | 8 | 8 | 8 | 8 | 8 | 8 | 8 | 8 | 8 | 8 | 8 | 8 |  |  |  |
| patient 6 month assessment |  |  |  |  |  |  | 8 | 8 | 8 | 8 | 8 | 8 | 8 | 8 | 8 | 8 | 8 | 8 |
| total assessments + training | 12 | 12 | 12 | 20 | 20 | 20 | 28 | 28 | 28 | 28 | 28 | 28 | 16 | 16 | 16 | 8 | 8 | 8 |
|  |  |  |  |  |  |  |  |  |  |  |  |  |  |  |  |  |  |  |
| **Total patients experiencing telecare system** | | | **48** |  |  |  |  |  |  |  |  |  |  |  |  |  |  |  |

| **Counties** |  |  |  |  |  |  |  |  |  |  |  |  |  |  |  |  |  |  |
| --- | --- | --- | --- | --- | --- | --- | --- | --- | --- | --- | --- | --- | --- | --- | --- | --- | --- | --- |
|  |  |  |  |  |  |  |  |  |  |  |  |  |  |  |  |  |  |  |
| Patient numbers in active and control arm, with tallies for clinical load, equipment numbers, researcher load | | | | | | | | |  |  |  |  |  |  |  |  |  |  |
| **equipment used 4 times, 3 months per patient** | | |  |  |  |  |  |  |  |  |  |  |  |  |  |  |  |  |
| recycle equipment starts Jun 10 | |  |  |  |  |  |  |  |  |  |  |  |  |  |  |  |  |  |
|  |  |  |  |  |  |  |  |  |  |  |  |  |  |  |  |  |  |  |
|  | Mar-10 | Apr-10 | May-10 | Jun-10 | Jul-10 | Aug-10 | Sep-10 | Oct-10 | Nov-10 | Dec-10 | Jan-11 | Feb-11 | Mar-11 | Apr-11 | May-11 | Jun-11 | Jul-11 | Aug-11 |
| **Clinical load** |  |  |  |  |  |  |  |  |  |  |  |  |  |  |  |  |  |  |
| recruitment total | 8 | 8 | 8 | 8 | 8 | 8 | 8 | 8 | 8 | 8 | 8 | 8 |  |  |  |  |  |  |
| recruitment to intervention | 4 | 4 | 4 | 4 | 4 | 4 | 4 | 4 | 4 | 4 | 4 | 4 |  |  |  |  |  |  |
| intervention total current | 4 | 8 | 12 | 12 | 12 | 12 | 12 | 12 | 12 | 12 | 12 | 12 | 8 | 4 |  |  |  |  |
|  |  |  |  |  |  |  |  |  |  |  |  |  |  |  |  |  |  |  |
| **Equipment load** |  |  |  |  |  |  |  |  |  |  |  |  |  |  |  |  |  |  |
| equipment in use | 4 | 8 | 12 | 12 | 12 | 12 | 12 | 12 | 12 | 12 | 12 | 12 | 8 | 4 |  |  |  |  |
|  |  |  |  |  |  |  |  |  |  |  |  |  |  |  |  |  |  |  |
| **Researcher load** |  |  |  |  |  |  |  |  |  |  |  |  |  |  |  |  |  |  |
| new patient training | 4 | 4 | 4 | 4 | 4 | 4 | 4 | 4 | 4 | 4 | 4 | 4 |  |  |  |  |  |  |
| patient baseline assessment | 8 | 8 | 8 | 8 | 8 | 8 | 8 | 8 | 8 | 8 | 8 | 8 |  |  |  |  |  |  |
| patient 3 month assessment |  |  |  | 8 | 8 | 8 | 8 | 8 | 8 | 8 | 8 | 8 | 8 | 8 | 8 |  |  |  |
| patient 6 month assessment |  |  |  |  |  |  | 8 | 8 | 8 | 8 | 8 | 8 | 8 | 8 | 8 | 8 | 8 | 8 |
| total assessments + training | 12 | 12 | 12 | 20 | 20 | 20 | 28 | 28 | 28 | 28 | 28 | 28 | 16 | 16 | 16 | 8 | 8 | 8 |
|  |  |  |  |  |  |  |  |  |  |  |  |  |  |  |  |  |  |  |
| **Total patients experiencing telecare system** | | | **48** |  |  |  |  |  |  |  |  |  |  |  |  |  |  |  |

| **Canterbury** |  |  |  |  |  |  |  |  |  |  |  |  |  |  |  |  |  |  |
| --- | --- | --- | --- | --- | --- | --- | --- | --- | --- | --- | --- | --- | --- | --- | --- | --- | --- | --- |
|  |  |  |  |  |  |  |  |  |  |  |  |  |  |  |  |  |  |  |
| Patient numbers in active and control arm, with tallies for clinical load, equipment numbers, researcher load | | | | | | | | |  |  |  |  |  |  |  |  |  |  |
| **equipment used 2 times, 6 months per patient** | | |  |  |  |  |  |  |  |  |  |  |  |  |  |  |  |  |
| recycle equipment starts Sep 10 | |  |  |  |  |  |  |  |  |  |  |  |  |  |  |  |  |  |
|  |  |  |  |  |  |  |  |  |  |  |  |  |  |  |  |  |  |  |
|  | Mar-10 | Apr-10 | May-10 | Jun-10 | Jul-10 | Aug-10 | Sep-10 | Oct-10 | Nov-10 | Dec-10 | Jan-11 | Feb-11 | Mar-11 | Apr-11 | May-11 | Jun-11 | Jul-11 | Aug-11 |
| **Clinical load** |  |  |  |  |  |  |  |  |  |  |  |  |  |  |  |  |  |  |
| recruitment total | 8 | 8 | 8 | 8 | 8 | 8 | 8 | 8 | 8 | 8 | 8 | 8 |  |  |  |  |  |  |
| recruitment to intervention | 4 | 4 | 4 | 4 | 4 | 4 | 4 | 4 | 4 | 4 | 4 | 4 |  |  |  |  |  |  |
| intervention total current | 4 | 8 | 12 | 16 | 20 | 24 | 24 | 24 | 24 | 24 | 24 | 24 | 20 | 16 | 12 | 8 | 4 |  |
|  |  |  |  |  |  |  |  |  |  |  |  |  |  |  |  |  |  |  |
| **Equipment load** |  |  |  |  |  |  |  |  |  |  |  |  |  |  |  |  |  |  |
| equipment in use | 4 | 8 | 12 | 16 | 20 | 24 | 24 | 24 | 24 | 24 | 24 | 24 | 20 | 16 | 12 | 8 | 4 |  |
|  |  |  |  |  |  |  |  |  |  |  |  |  |  |  |  |  |  |  |
| **Researcher load** |  |  |  |  |  |  |  |  |  |  |  |  |  |  |  |  |  |  |
| new patient training | 4 | 4 | 4 | 4 | 4 | 4 | 4 | 4 | 4 | 4 | 4 | 4 |  |  |  |  |  |  |
| patient baseline assessment | 8 | 8 | 8 | 8 | 8 | 8 | 8 | 8 | 8 | 8 | 8 | 8 |  |  |  |  |  |  |
| patient 3 month assessment |  |  |  | 8 | 8 | 8 | 8 | 8 | 8 | 8 | 8 | 8 | 8 | 8 | 8 |  |  |  |
| patient 6 month assessment |  |  |  |  |  |  | 8 | 8 | 8 | 8 | 8 | 8 | 8 | 8 | 8 | 8 | 8 | 8 |
| total assessments + training | 12 | 12 | 12 | 20 | 20 | 20 | 28 | 28 | 28 | 28 | 28 | 28 | 16 | 16 | 16 | 8 | 8 | 8 |
|  |  |  |  |  |  |  |  |  |  |  |  |  |  |  |  |  |  |  |
| **Total patients experiencing telecare system** | | | **48** |  |  |  |  |  |  |  |  |  |  |  |  |  |  |  |

| **Tairawhiti** |  |  |  |  |  |  |  |  |  |  |  |  |  |  |  |  |  |  |
| --- | --- | --- | --- | --- | --- | --- | --- | --- | --- | --- | --- | --- | --- | --- | --- | --- | --- | --- |
|  |  |  |  |  |  |  |  |  |  |  |  |  |  |  |  |  |  |  |
| Patient numbers in active arm, with tallies for clinical load, equipment numbers, researcher load (no control arm) | | | | | | | | |  |  |  |  |  |  |  |  |  |  |
| **equipment used 2 times, 6 months per patient** | | |  |  |  |  |  |  |  |  |  |  |  |  |  |  |  |  |
| recycle equipment starts Sep 10 | |  |  |  |  |  |  |  |  |  |  |  |  |  |  |  |  |  |
|  |  |  |  |  |  |  |  |  |  |  |  |  |  |  |  |  |  |  |
|  | Mar-10 | Apr-10 | May-10 | Jun-10 | Jul-10 | Aug-10 | Sep-10 | Oct-10 | Nov-10 | Dec-10 | Jan-11 | Feb-11 | Mar-11 | Apr-11 | May-11 | Jun-11 | Jul-11 | Aug-11 |
| **Clinical load** |  |  |  |  |  |  |  |  |  |  |  |  |  |  |  |  |  |  |
| recruitment | 2 | 2 | 2 | 2 | 2 | 2 | 2 | 2 | 2 | 2 | 2 | 2 |  |  |  |  |  |  |
|  |  |  |  |  |  |  |  |  |  |  |  |  |  |  |  |  |  |  |
| intervention total current | 2 | 4 | 6 | 8 | 10 | 12 | 12 | 12 | 12 | 12 | 12 | 12 | 10 | 8 | 6 | 4 | 2 |  |
|  |  |  |  |  |  |  |  |  |  |  |  |  |  |  |  |  |  |  |
| **Equipment load** |  |  |  |  |  |  |  |  |  |  |  |  |  |  |  |  |  |  |
| equipment in use | 2 | 4 | 6 | 8 | 10 | 12 | 12 | 12 | 12 | 12 | 12 | 12 | 10 | 8 | 6 | 4 | 2 |  |
|  |  |  |  |  |  |  |  |  |  |  |  |  |  |  |  |  |  |  |
| **Researcher load** |  |  |  |  |  |  |  |  |  |  |  |  |  |  |  |  |  |  |
| new patient training | 2 | 2 | 2 | 2 | 2 | 2 | 2 | 2 | 2 | 2 | 2 | 2 |  |  |  |  |  |  |
| patient baseline assessment | 2 | 2 | 2 | 2 | 2 | 2 | 2 | 2 | 2 | 2 | 2 | 2 |  |  |  |  |  |  |
| patient 3 month assessment |  |  |  | 2 | 2 | 2 | 2 | 2 | 2 | 2 | 2 | 2 | 2 | 2 | 2 |  |  |  |
| patient 6 month assessment |  |  |  |  |  |  | 2 | 2 | 2 | 2 | 2 | 2 | 2 | 2 | 2 | 2 | 2 | 2 |
| total assessments + training | 4 | 4 | 4 | 6 | 6 | 6 | 8 | 8 | 8 | 8 | 8 | 8 | 4 | 4 | 4 | 2 | 2 | 2 |
|  |  |  |  |  |  |  |  |  |  |  |  |  |  |  |  |  |  |  |
| **Total patients experiencing telecare system** | | | **24** |  |  |  |  |  |  |  |  |  |  |  |  |  |  |  |

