# Study Design

ASSET will be conducted as:

- **Three separate randomised controlled trials** in Auckland, Counties Manukau and Canterbury (there will be no control group in Tairawhiti)
- Within each of the active intervention arms, including Tairawhiti, there will be an **action research process to optimise the telecare system intervention.**
- Within each control arm there will be a **process of mapping real usual care.**

Each region will stand alone as a discrete trial though with some shared outcomes. Standard criteria and measures will apply across all trials.

The telecare equipment will be available to all four health services for 12 months, with equipment loaned to any one patient for up to three months.

Participants will be assessed at baseline with follow up at three (immediately post intervention) and six months (three months post intervention).

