# Eligibility

**Inclusion criteria:**

1. *All areas*
   1. age 16+
   2. living permanently at home
   3. expected to be available for 3 months
   4. expected to survive study period
   5. able to communicate in English (or someone in household able to translate)
   6. able to physically manage the equipment (or someone available to assist)
2. A*uckland* – Permanently resides in the Auckland DHB region, current or recent in-patient to Auckland City Hospital with heart failure as the primary reason for admission
3. *Counties Manukau* – Permanently resides in the Counties Manukau DHB region, enrolled with ProCare PHO, current or recent in-patient at Middlemore Hospital with COPD as the primary reason for admission
4. *Tairawhiti* – Permanently resides in the Tolaga Bay area, enrolled with Ngati Porou Hauora PHO, and is on the PHO chronic condition management programme
5. *Canterbury* – Permanently resides in the Canterbury DHB region, enrolled with practices working with the community specialist respiratory service, with COPD being treated with Long Term Oxygen Therapy (LTOT) at home

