# Optimising the Intervention

The chosen approach is action research (AR). For those not familiar with this method, it is a cyclical process of plan, act, reflect and learn, and adapt the planned activities to enhance the final outcome of what we endeavour to achieve 10. It is broader than a ‘plan do study act’ quality improvement cycle. Its mixed heritage includes anthropological campaigns that sought to challenge social structures by using research understanding to empower the least powerful in society. More pragmatically, the processes have proven useful to iteratively clarify the requirements and concerns of those involved in deploying or using new technologies.

Action research implies cycles and iterations of learning and application 10 11. For the ASSET project action research will be used as follows:

- The current project defined as the exploration of telemonitoring in New Zealand, and as formative pilot study for future randomised clinical trials on telemonitoring, is the primary and encompassing AR cycle, and
- Each three month allocation of telemonitoring for a patient will be considered a cycle of planning, acting and learning.

AR also implies that a problem has been identified, is being clarified and resolved 10. For three DHBs the clinicians and healthcare service providers have identified a chronic condition management issue that telemonitoring could contribute to with positive outcomes, while Tairawhiti DHB has a different approach. The Tairawhiti community will be invited to participate with clinicians and service providers to identify the problem/s for which telemonitoring could contribute a solution.

More specifically, the researchers will:

- observe those using the technologies, primarily the clinical nurse specialists, patients / whanau, each for about 4 periods of one hour over 3 months
- conduct semi-structured interviews with each at the beginning and end of the intervention
- iteratively review their findings with each party at the end of each observation period
- record changes they observe as the intervention is refined
- seek to establish and document consensus on an algorithm of care the CNS will use for a further trial

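### The telecare loan is capped at three months in the design but runs six months in the Canterbury and Tairawhiti schedules, so Canterbury's follow-up visits do not measure what the design says they do

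*Protocol*

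**What the plan says.** The Study Design section speaks for every site. It opens the point with "The telecare equipment will be available to all four health services for 12 months" and adds the limit "with equipment loaned to any one patient for up to three months". It then places the assessments: "follow up at three (immediately post intervention) and six months (three months post intervention".

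Other sections use the same length:
- Eligibility, criteria for all areas: "expected to be available for 3 months".
- Optimising the Intervention: "Each three month allocation of telemonitoring for a patient will be considered a cycle of planning, acting and learning".
- Qualitative interviews puts the technology interview in the third month of kit use, while Appendix 3 puts it at the end of telemonitoring. The two agree only if the loan lasts three months.

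Appendix 8 splits the sites. Auckland and Counties Manukau are headed "equipment used 4 times, 3 months per patient". Canterbury and Tairawhiti are headed "equipment used 2 times, 6 months per patient". All four tables schedule assessments at 3 and 6 months.

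On analysis, Study Design and Sample size describe each region as a trial in its own right. The Analysis section describes mixed models with site as a fixed effect and takes the main result for the scales from the group-by-time interaction. Nothing in the protocol explains or permits a loan length that differs by site.

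**The concern.** Loan length fixes what each follow-up visit means. With a three-month loan, month 3 shows the effect at the end of telecare and month 6 shows whether it lasts after the kit is returned. With a six-month loan, month 3 is a midpoint and month 6 is the end of treatment, so nothing is observed after return.

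Two things are at stake. Within Canterbury, a month-6 difference could be reported as persisting three months after telecare when patients have only just finished it. Across sites, a combined month-6 estimate would average two different quantities under one label. A site main effect removes differences in level between sites. It does not remove a difference between sites in what the time point represents.

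The planned exposure also differs, and kit time feeds the depreciation and monitoring costs listed under Measuring costs.

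**Working it through.** **Step 1: is six months a slip in a header line?** The inputs are the Appendix 8 monthly recruitment to the intervention (4 a month in Auckland, Counties Manukau and Canterbury; 2 a month in Tairawhiti; 12 recruiting months from Mar-10) and a loan of L months.

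Kits in use in month m = sum of recruits in months m−L+1 to m. Uses per kit = total recruits / peak kits.

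| Site | L | Computed row | Matches Appendix 8? | Uses per kit |
|---|---|---|---|---|
| Auckland, Counties Manukau | 3 | 4, 8, 12 (×10), 8, 4 | yes | 48/12 = 4 |
| Canterbury | 3 | 4, 8, 12 (×10), 8, 4 | no | 48/12 = 4 |
| Canterbury | 6 | 4, 8, 12, 16, 20, 24 (×7), 20, 16, 12, 8, 4 | yes | 48/24 = 2 |
| Tairawhiti | 3 | 2, 4, 6 (×10), 4, 2 | no | 24/6 = 4 |
| Tairawhiti | 6 | 2, 4, 6, 8, 10, 12 (×7), 10, 8, 6, 4, 2 | yes | 24/12 = 2 |

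The recycling dates agree: Jun 10 is three months after the Mar-10 start, and Sep 10 is six. The six-month loan is therefore built into both schedules. For Canterbury it means 48 × 6 = 288 kit-months, against 48 × 3 = 144 under the Study Design limit.

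**Step 2: what the visits mean under Appendix 8.**

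| Site | Month 3 | Month 6 |
|---|---|---|
| Auckland, Counties Manukau | end of telecare | three months off telecare |
| Canterbury, Tairawhiti | midpoint of telecare | end of telecare |

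The Study Design labels fit the first row and fail in the second. The protocol's summary table of data collection places the second round of scales at the end of each patient's telemonitoring, which would be month 3 in Auckland and month 6 in Canterbury.

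**Step 3: how many randomised patients.** Tairawhiti has no control arm, so the randomised site affected is Canterbury: 48 / (48 + 48 + 48) = 48/144, one third of the planned randomised intervention patients.

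**Step 4: illustration of pooling at month 6.** Assume a 10-point SF-36 effect during use (the target difference under Sample size, not an expected effect), a fraction c of it persisting three months after return, equal site weights and equal attrition. The protocol gives no value for c.

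Pooled month-6 difference = 10 × (1/3) + 10c × (2/3). The true difference three months off telecare = 10c.

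| c | Pooled | True off-telecare | Excess from Canterbury |
|---|---|---|---|
| 0 | 3.3 | 0 | 3.3 |
| 0.5 | 6.7 | 5.0 | 1.7 |
| 1 | 10 | 10 | 0 |

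**The case against.** **Stand-alone trials.** If each region is analysed alone, as Study Design and Sample size say, nothing is mixed across sites. This has force: the pooling harm exists only if the site term in the Analysis section describes the model actually used. It does not remove the contradiction within Canterbury, whose visits still would not fit the design labels.

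**Month 3.** A reader might infer that the 3-month comparison is spoiled too. It largely is not. By month 3 every intervention patient has had about three months of telecare under either schedule. The label is wrong for Canterbury, but exposure to date is the same. The substantive difference is at month 6.

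**The 12-month availability.** A reader might also infer that Appendix 8 breaks the 12-month limit, because kits are in use in 14 calendar months at Auckland and Counties Manukau and 17 at Canterbury and Tairawhiti, and hence that the planned numbers cannot be reached. The documents do not establish this. Kit-months over peak kits give 144/12 = 12 at each of Auckland and Counties Manukau, 288/24 = 12 at Canterbury and 144/12 = 12 at Tairawhiti. Each kit serves exactly 12 months, and the longer spans come from staggered starts. Study Design does not say that all kits must be issued and returned within one calendar year. At most the wording is ambiguous.

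**Pilot status.** The protocol says it collects pilot data and is not powered to confirm effectiveness for most outcomes, and the conflict sits in a workload appendix with one randomised site affected. That limits the consequences. Pilot effect sizes are nevertheless meant to inform later trials, and they need a clear time point.

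**Conclusion.** The contradiction is real. Study Design limits the loan to three months for all four services, with support from Eligibility and Optimising the Intervention, while Appendix 8 plans six months in Canterbury and Tairawhiti in a way that only a six-month loan reproduces. Both cannot be followed.

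If Appendix 8 is followed, the randomised Canterbury trial has no post-intervention assessment, and its month-6 result is an end-of-telecare result. That conclusion needs no assumption beyond the schedule itself.

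The effect on a combined analysis is conditional. It requires that sites be pooled and that the effect fade after return. The 3.3 points is the upper end of the illustration, with a 10-point effect, no carry-over and equal site weights; the distortion shrinks to zero with full carry-over. It is not an estimate of bias in this trial.

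**What to change.** Reconcile Study Design, Eligibility, Optimising the Intervention and the Canterbury and Tairawhiti tables of Appendix 8 so that each site has one stated loan length. Which length is right is for the sponsor and investigators to decide. Then:

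- If the stated length is three months everywhere, revise the Canterbury and Tairawhiti tables. The visit labels can stay.
- If the lengths differ by site, say so in Study Design, correct the visit labels for the sites concerned, and define assessments relative to the end of each site's loan. Do not pool month-6 results across sites with different loan lengths.
- In either case, state in the Analysis section how the site term fits with stand-alone trials.
- Clarify whether the 12 months of equipment availability is per kit or a calendar window.

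The cost is protocol wording and a revised appendix. Only if a longer loan is confirmed and an assessment after return is still wanted would a later visit, with its researcher time, be needed at those sites.
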